### Objectives

Objective evaluation of the comparative effectiveness, safety, and economic evaluation of *Chuna* manual therapy for application in cost-effective, evidence-based practice are important issues both for the Korean medicine sector and for national health services improvement. High-quality RCTs are warranted for rigorous assessment of *Chuna* effectiveness, safety, and cost-effectiveness. The hypotheses of this study are as follows: (1) *Chuna* manual therapy will be more effective and safer than (or equally safe as) conventional usual care in nonacute LBP patients and (2) concurrent treatment consisting of *Chuna* manual therapy and usual care will be more effective than *Chuna* alone or conventional usual care alone in nonacute LBP patients. Therefore, the objectives of this pCRN (pilot *Chuna* Research Network) study are to investigate the following in nonacute LBP patients: (1) the comparative effectiveness and safety of *Chuna* manual therapy compared to conventional usual care through comparison of pain, functionality, quality of life parameters and adverse events, (2) the effectiveness and safety of a concurrent treatment consisting of *Chuna* manual therapy and usual care, which is reflective of actual clinical practice, through comparison of two single treatment groups of *Chuna* manual therapy and usual care, and a combined treatment group of *Chuna* manual therapy with usual care and (3) costs and effectiveness (utility) data of the three groups for exploratory cost-effectiveness analysis (economic evaluation). However, if the current sample size deters this pilot study from reaching a definite conclusion regarding aims (1), (2), and (3), the main objectives of this preliminary study will be to determine a sample size appropriate for statistical testing in future large-scale studies and to assess the feasibility of a full-scale multicenter trial.

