### Adverse events

Physicians will monitor and record any unexpected or unintended patient reaction to *Chuna*, usual care, or its combination at each visit. Adverse events (AEs) associated with *Chuna* will include, but not be limited to, AEs anticipated from previous reports of manual therapy and will stay open to all possibilities taking into consideration other potential, unknown AEs. Physicians will rate the causal relationship between each treatment method and AE occurrence on a 6-point scale (1 = definitely related; 2 = probably related; 3 = possibly related; 4 = probably not related; 5 = definitely not related; and 6 = unknown), and all AEs will be categorized into three levels using the Spilker classification (mild (1) = not needing additional intervention, nor significantly inhibiting to the normal lifestyle (function) of the participant; moderate (2) = significantly inhibiting to the normal lifestyle (function) of the participant, and may need additional intervention, recovering afterwards; and severe (3) = severe AE requiring intensive intervention, and leaving sequelae). In the case of “serious adverse event (SAE)” during study duration, unblinding is permissible and the relevant Institutional Review Board (IRB) and main study site (Pusan National University Korean Medicine Hospital) will be informed and will decide whether the trial will continue or be terminated. In the event that a subject suffers direct injury associated with the clinical trial, the subject may receive appropriate medical action as seen fit by the subinvestigator, and damage compensation will follow prespecified clinical research insurance clauses. All study participants will be provided with an emergency contact number to the principal investigator or subinvestigator for any questions, medical issues or research-related diseases during the study and accordingly receive requested services.

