### Data monitoring and safety monitoring

This study is a pilot study with no interim analysis, and a data monitoring committee was not organized as no SAEs regarding *Chuna* or usual care not previously reported are expected to occur.

Safety assessment will mainly assess frequency of AEs, including all SAEs. AE reports will summarize the number and percentage of participants who experienced AEs, and will include categorized information on body region of AE manifestation. Other data (e.g., severity, causal relationship with treatment) will be included in safety monitoring reports.

An outside CRO will be entrusted with safety and data monitoring. CRO monitoring will consist of three sessions in the following order: initiative monitoring at first subject enrollment, one midterm monitoring during the clinical trial, and conclusive monitoring upon completion of clinical trial. Participant safety data and CRF and source documents will be reviewed and crosschecked to confirm participant safety and data integrity.

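### The three adverse event severity levels do not cover all events and tie the severe grade to sequelae, so the severity table may understate grade 3 events

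*Protocol article*

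**What the plan says.** Under Adverse events, the protocol article states that "all AEs will be categorized into three levels using the Spilker classification". It then prints the levels in full:

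- The lowest level is given as "mild (1) = not needing additional intervention, nor significantly inhibiting to the normal lifestyle (function) of the participant".
- For the middle level, the article asks for limited function with a good outcome: "moderate (2) = significantly inhibiting to the normal lifestyle (function) of the participant, and may need additional intervention, recovering afterwards".
- The top level sets two conditions at once: "severe (3) = severe AE requiring intensive intervention, and leaving sequelae".

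Under Objectives, the first hypothesis includes safety: Chuna is expected to be "more effective and safer than (or equally safe as) conventional usual care".

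Data monitoring and safety monitoring says how the data will be used. "Safety assessment will mainly assess frequency of AEs, including all SAEs", and "AE reports will summarize the number and percentage of participants who experienced AEs". Severity comes after that: "Other data (e.g., severity, causal relationship with treatment) will be included in safety monitoring reports". The handling of SAEs (Adverse events) and the Stopping rules section both refer to SAEs and do not mention the three levels.

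**The concern.** A severity scale that must hold every event should give each event exactly one grade, and the grade should describe how bad the event was, not how it ended. This scale does neither.

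Severe joins intensive intervention and sequelae with *and*, so full recovery takes an event out of the top level whatever treatment it needed. Moderate requires recovery, so a function-limiting event that leaves sequelae without intensive treatment fits neither moderate nor severe. An event that needs some extra treatment but does not significantly limit function is neither mild nor moderate, and that is not an exotic case. The severe definition also uses the word severe to define itself, so it gives a rater little help with a case in the gaps.

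At stake is the severity tabulation, which is a planned safety output in a four-site trial with a safety hypothesis. Treating physicians cannot be blinded (Blinding) and record the AEs. Events in the gaps have to be placed by judgement, which may differ between raters.

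**Working it through.** The article states no figure that depends on the scale, so there is none to reproduce. The check applies the three printed definitions literally to every logical combination.

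**Inputs** (all from Adverse events)
- Mild: no additional intervention AND no significant inhibition.
- Moderate: significant inhibition AND recovery; intervention optional.
- Severe: intensive intervention AND sequelae.

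**Combinations:** 3 intervention levels × 2 (function) × 2 (outcome) = 12.

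| Intervention | Function significantly inhibited | Outcome | Grade as printed | Grade after the fix |
|---|---|---|---|---|
| None | No | Recovery | Mild | Mild |
| None | No | Sequelae | Mild | Mild |
| None | Yes | Recovery | Moderate | Moderate |
| None | Yes | Sequelae | **No grade** | Moderate |
| Additional | No | Recovery | **No grade** | Moderate |
| Additional | No | Sequelae | **No grade** | Moderate |
| Additional | Yes | Recovery | Moderate | Moderate |
| Additional | Yes | Sequelae | **No grade** | Moderate |
| Intensive | No | Recovery | **No grade** | Severe |
| Intensive | No | Sequelae | Severe | Severe |
| Intensive | Yes | Recovery | Moderate | Severe |
| Intensive | Yes | Sequelae | Severe | Severe |

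**Result as printed:** 2 mild + 3 moderate + 2 severe + 5 without a grade = 12.

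**Result after the fix:** 2 mild + 6 moderate + 4 severe = 12, none ungraded. Six rows change: the five ungraded rows gain a grade, and one moves from moderate to severe.

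**Sensitivity to the reading**
- The table lets moderate include intensive intervention. If moderate stops at additional intervention, the intensive, inhibiting, resolved event also loses its grade: 2 mild, 2 moderate, 2 severe, 6 ungraded.
- If intensive intervention without significant inhibition is thought implausible, drop those two rows (one ungraded, one severe). Then 4 of the remaining 10 are ungraded.

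**Scale.** With 20 participants per arm (Sample size), moving one participant into or out of grade 3 changes that arm's proportion by 1/20 = 5 percentage points. That would be true under any scale, so it measures how sensitive the table is, not how large the error is. The 12 rows are logical cases, not expected shares of events.

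**The case against.** The strongest reply is that little rests on the scale. Safety is judged mainly by AE frequency, including all SAEs, and severity is listed only among other data. An ungraded or downgraded event is still an AE, and an SAE is still counted and reported. This stands.

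It disposes of several stronger inferences that a reader might draw:

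- *Severe harms are undercounted.* Only the grade 3 count is exposed. The article gives no AE rates, so an undercount is possible but not shown.
- *Serious events are hidden among moderate ones.* Severe and serious are different categories here, and SAEs follow their own path.
- *The safety comparison is biased.* The definitions are the same in all three arms, so no direction between arms follows. Grading by unblinded staff comes from the open design and would remain after rewording.
- *The severe grade cannot be assigned because sequelae are unknown at the visit.* The article does not say when a grade becomes final. Table 1 schedules AE assessment at every visit and at weeks 7, 10 and 14, so grades can be completed later.

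A second reply is that the scale is attributed to a published classification, and that the article may only paraphrase it. Whether the paraphrase is faithful cannot be checked here. Training and a standard operating procedure for completing the Case Report Form (CRF) exist (Data collection and management) but are not shown. This limits what can be said about the source and the CRF. It does not repair the printed rule, which claims to hold all AEs and does not. Because the definitions are printed in full, this is a rule stated badly, not detail left to a fuller document.

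**Conclusion.** The point holds in a limited form. As printed, the severity levels are not exhaustive and mix severity with outcome. Read literally, 5 of 12 combinations have no grade, and an intensively treated, function-limiting event that resolves is graded no higher than moderate. The grade 3 count in the severity tabulation may therefore be understated, and grading may vary between physicians. A low or zero grade 3 count would be hard to interpret.

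The effect stops there. AE frequency, SAE counts and the stopping rule are untouched, no between-arm direction follows, and the size cannot be computed. The conclusion assumes that the printed definitions are the ones applied, with *and* meaning that both conditions must hold. It is a modest defect that is cheap to correct.

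**What to change.** Define the grades by intervention and function only, so that every AE gets exactly one:

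- **Severe:** requires intensive intervention.
- **Moderate:** not severe, but needs additional intervention or significantly inhibits function.
- **Mild:** neither.

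Record outcome (recovered or sequelae) separately and tabulate it beside severity, so that lasting harm stays visible at every grade, including mild. Replacing *and* with *or* in the severe definition would not be enough, because outcome would remain part of the grade. State that the wording departs from the named classification.

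The cost is a change to the definitions and, if the CRF does not already match, to its AE page. No extra visits or staff are needed. Severe and moderate counts may look slightly less favourable, and there is a small loss of comparability with trials that use the named classification unchanged.

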### Data monitoring and safety monitoring

This study is a pilot study with no interim analysis, and a data monitoring committee was not organized as no SAEs regarding *Chuna* or usual care not previously reported are expected to occur.

Safety assessment will mainly assess frequency of AEs, including all SAEs. AE reports will summarize the number and percentage of participants who experienced AEs, and will include categorized information on body region of AE manifestation. Other data (e.g., severity, causal relationship with treatment) will be included in safety monitoring reports.

An outside CRO will be entrusted with safety and data monitoring. CRO monitoring will consist of three sessions in the following order: initiative monitoring at first subject enrollment, one midterm monitoring during the clinical trial, and conclusive monitoring upon completion of clinical trial. Participant safety data and CRF and source documents will be reviewed and crosschecked to confirm participant safety and data integrity.

### Stopping rules

The trial will be stopped in the case that the principle investigator regards that there is unacceptable risk of SAE(s) within group(s).

## Discussion

Usual care was selected as the choice of comparator in this study for investigation of the effectiveness and safety of *Chuna* manual therapy. Various national and international clinical practice guidelines and systematic reviews were consulted in discussion of usual care contents for LBP. While current guidelines indicate the benefits of conservative treatment [5], the evidence for individual conservative treatment methods and opinions on what should constitute standard care of LBP are somewhat inconsistent [4–6]. Moreover, recent reports state that the effect of acetaminophen, which is recommended for first-line use in LBP guidelines [4–6], is unclear [35]. Therefore, in this study we opted to use the most frequently used LBP treatments in Korea as opposed to an evidence-based selection. Korea has a unitary government-run national health insurance system which aims to cover the entire South Korean population and all medical institutions. This insurance system reimburses HIRA-approved medical costs for the greater majority of diseases including LBP, and the HIRA database contains extensive information on medication, medical services, and diagnosis [17]. For this study, we extracted the most frequently used treatment types in patients with a main diagnosis code of LBP from the 2011 HIRA national patients’ sample (NPS) data, and provided this list to usual care providers for reference in patient treatment in an effort to secure validity in usual care treatment selection.

While the updated Cochrane review on spinal manipulative therapies for chronic LBP covers many study designs similar to the current study comparing spinal manipulation with other treatments, such as usual care, or as an add-on treatment to other treatments, such as usual care alone, evidence for the effect of spinal manipulative therapy is not conclusive [36]. However, as *Chuna* manual therapy and the spinal manipulative therapies included in the Cochrane review hold distinct differences, clinical effects may also be disparate. Meanwhile, a 2013 systematic review of RCTs on *Chuna* published in the Korean *Chuna* literature states that the two RCTs related to LBP both support a significant effect of *Chuna*, but that they are limited by qualitative issues and small sample size [37]. Therefore, it can be inferred from these evaluations that further rigorous clinical studies on *Chuna*, a Korean spinal manipulative therapy, are in order.

The aim of this pCRN study is to examine the comparative clinical effectiveness of *Chuna*, a Korean spinal manual therapy, through comparison of *Chuna* manual therapy and usual care treatments most frequently used in Korea, and investigate whether the combined treatment of *Chuna* manual therapy and usual care, which is reflective of, and more frequently encountered, than singular treatment of *Chuna* or usual care in real-world clinical practice, is more effective than single treatment. While this pilot study may fail to reach a definite conclusion due to current sample size, it will still hold relevance as one of the first well-designed, rigorous RCTs on *Chuna* manual therapy for nonacute LBP patients, and provide preliminary effectiveness and safety monitoring results for future large-scale, multicenter RCTs.

### Trial status

Participant recruitment is anticipated to be from March to August 2016, and study completion to be reported in December 2016. The full-scale, multicenter RCT (CRN study) is expected to be initiated in 2017 after analysis of pCRN data.

## Abbreviations

AE: Adverse event
ANCOVA: Analysis of covariance
ANOVA: Analysis of variance
CMT: *Chuna* manual therapy
CRF: Case Report Form
CRIS: Clinical Research Information Service
CRO: Contract research organization
EQ-5D: EuroQol-5 dimensions
HIRA: Health Insurance Review and Assessment
HUI-III: Health Utility Index III
IRB: Institutional Review Board
KMD: Korean medicine doctor
LBP: Low back pain
LOCF: Last observation carried forward
NPS: National patients’ sample
NRS: Numeric Rating Scale
ODI: Oswestry Disability Index
pCRN: Pilot *Chuna* Research Network
PGIC: Patient Global Impression of Change
QALY: Quality-adjusted life years
RCT: Randomized controlled trial
ROM: Range of movement
SAE: Serious adverse event
SD: Standard deviation
SMT: Spinal manipulative therapy
SOP: Standard operating procedure
SPIRIT: Standard Protocol Items: Recommendations for Interventional Trials
SR: Systematic review
UC: Usual care
